## Abstract

**Abstract:**

**Introduction:**

Digital inclusion (which includes skills, accessibility and connectivity to the internet and digital devices) is a ‘super social determinant of health’ because it affects many aspects of life that influence health. Older people are especially vulnerable to digital exclusion. Existing digital inclusion interventions are commonly offered opportunistically to people who come into contact with services, or in specific locations. The lack of systematic identification of need unintentionally excludes older people who may be most in need of support, and that support is not addressing their needs.

**Methods and analysis:**

This multi-method project includes six workstreams: (1) A survey of people aged 65+ to ask about digital use and engagement. Survey data will be used to develop a model that predicts digital exclusion from data available in primary care records. (2) Testing, via a further survey, the external validity of the model to identify those who are digitally excluded. (3) Interviews with community service providers to identify, understand and define the components of existing digital inclusion services for older people. Concurrently, a rapid review of the literature will identify evidence for interventions aimed at supporting digitally excluded adults aged 65+. (4) Interviews with people aged 65+ representing a range of digital use will explore factors from the COM-B model that influence digital behaviours—their capability (C), opportunity (O) and motivation (M) relating to digital engagement. Analysis outputs will identify the intersectional nature of barriers or facilitators to digital inclusion. (5) Co-production workshops with older people and community service providers will identify key components of interventions that are required to address digital exclusion. Components will be mapped against existing interventions, and the ‘best fit’ intervention(s) refined. An implementation plan will be developed in parallel. (6) Feasibility testing of the refined intervention(s) to assess acceptability and obtain feedback on content and delivery mechanisms.

**Ethics and dissemination:**

This study was approved by the Yorkshire & The Humber - Bradford Leeds Research Ethics Committee on 23 October 2023 (ref. 23/YH/0234). Findings will be disseminated in academic journals and shared at webinars, seminars, conferences and events arranged by organisations operating across the digital inclusion and older people fields.

**Trial registration:**

https://www.isrctn.com/ISRCTN18306736

STRENGTHS AND LIMITATIONS OF THIS STUDYThe study team are working with general practitioner (GP) practices that include some of the least and most deprived populations in the UK, inclusive of a range of minority ethnic groups, thus ensuring that findings will have relevance across the UK population.A key output of the work will be a model, using routine GP data, to support identification of older people who are digitally excluded. The methodology developed may be appropriate for replication for identification of other hardly-reached groups.Qualitative interviews and workshops will be focused on an in-depth understanding of digital exclusion, and associated behaviours and factors that influence digital behaviours, to provide a comprehensive understanding of what the intervention(s) we develop should target.The study team’s strong links with GP practices, local authorities and the community are facilitating recruitment and engagement and will provide direct routes for dissemination.While we endeavour to maximise diversity of inclusion in our study population, we are working in one region of the UK (Yorkshire) so there may be variations in the population in other areas of the UK that we do not capture.

## Introduction

 Digital exclusion is a super social determinant of health^1 2^ that affects a number of different areas of life that influence our health and well-being. These areas include: finance (online banking, benefits guidance); physical and social environment (online tickets for trains, parking, cultural events); health and social care (access to e-consultations and remote/online healthcare, online appointment booking systems, internet-based information about health, social care and housing); and online interaction with family members who do not live locally. There is a widening gap between those who can and cannot (or do not) use technology, which was hastened by the increased use of technology in our everyday activities during the COVID-19 pandemic. While there is no universally recognised definition of digital exclusion,^3^ the term typically describes those who do not have access to or capability to use the internet and are missing out by not being online,^4^ or whose limited online activity or digital skills mean they do not fully participate in modern society.^3 5^

Digital exclusion has the most negative impact on older people (eg, it can contribute to loneliness, poor housing and poor health); however, older people are the group most often excluded from digital activities,^6^,^9^ with 31% of over 65s not having an internet connection at home, compared with 4% among those aged 35–44.^3^ Among older people, digital exclusion is reportedly higher in lone households, those of Asian ethnicity and females, with these inequalities appearing to increase with age.^10 11^ Income and socioeconomic disadvantage have also been associated with digital exclusion, although this has not been examined by age.

Numerous reports (eg,^12^,^19^) have highlighted the extent and challenges of digital exclusion, but prevalence data has been derived from national surveys, which have inherent weaknesses (eg, they are often not granular enough to provide detail on the nuances of people’s lives),^20^ and there is no current, systematic method to identify those who are digitally excluded^21^ at a local population level. More focused work to identify barriers and facilitators to digital inclusion has overwhelmingly relied on convenience sampling,^20^ usually people already in receipt of services or self-identifying as requiring support. These approaches do not reliably identify the ‘hardly reached’ older person who may be most in need.

Third sector organisations have developed digital inclusion interventions to address the needs of their local populations, but access to this digital support is often reliant on third party or self-referrals, or geographical location as a ‘best guess’ of the digitally excluded population,^22^ while evidence of success is often anecdotal.^20^ Thus, there is likely to be a ‘hidden’ population of older people who are digitally excluded^7^ who are not known to support services and therefore support available is not tailored to their needs. The evidence review from the Digital Poverty Alliance^20^ identifies that ‘comparatively little academic evidence on the digital divide comes from qualitative studies, lived experience or co-produced research with people who experience digital poverty in the UK’, and highlights the need for community level data. In line with their recommendations, we will develop a systematic identification process; explore through qualitative interviews the determinants and intersectional nature of digital exclusion; gain insight and understanding from third sector groups; and co-produce with the hardly reached digitally excluded population tailored interventions to address their needs.

## Methods and analysis

### Study aims and objectives

The overarching aim of this research is to develop a robust, replicable identification system for digitally excluded older adults; and, working with community groups and those who are digitally excluded, refine and feasibility test an intervention (or interventions) to improve digital inclusion opportunities for those currently excluded.

Study objectives are to:

A. Identify those who are digitally excluded:

Survey methods will be used to estimate prevalence and predictors of digital exclusion in those aged 65+. Using this survey data, we will then use a predictive modelling approach that is implementable in primary care systems to systematically identify older people (aged 65+) at risk of digital exclusion or who are digitally excluded.Feasibility test our method of identifying those who are digitally excluded from primary healthcare registers.

B. Refine an intervention to meet their needs:

Identify the content, format and purpose of existing digital inclusion interventions through regional community consultation, and undertake a rapid review of the literature to understand the emerging evidence for digital training/support interventions for older people.Explore through interviews with a sample of older people the determinants and intersectional nature of digital exclusion.Undertake a series of co-production workshops—involving digitally included and excluded older people, and service providers—to identify and develop key components of an intervention(s) that would engage those who are currently digitally excluded (considering also how the intervention would be implemented in practice).

C. Feasibility test the intervention:

Provision of the newly-developed intervention to digitally excluded older people—to ascertain inclusion, feasibility, acceptability and inform intervention refinement (its content and how it is provided).

### Design summary

This multi-method study, taking a pragmatic world view^23^ and having consideration for the Medical Research Council guidance for developing and evaluating complex interventions,^24^ comprises six workstreams which align with the above objectives. See figure 1 for a summary of these workstreams.

**Figure 1 F1:**
[figure not shown]
Study flowchart. GP, general practitioner.

### Setting

Two general practitioner (GP) practices will be selected to take part in the first survey, and a further one to two practices in the second survey (workstreams 1 and 2). The number of practices selected to be determined by numbers of older people on practice registers and the required sample size. Primary care health registers provide the most inclusive population record available, so GP practices are the most suitable setting for survey distribution. We will work with practices that include some of the least and most socioeconomically disadvantaged populations in the UK, those with varying age profiles, and will ensure that our sample includes people from a range of minority ethnic backgrounds and from both urban and rural areas.

Scoping work with community service providers (workstream 3) will mostly take place remotely via telephone or video call, possibly with some visits to the organisations. Interviews with older people (workstream 4) will take place in participants’ homes or another community location of their choice. Co-production workshops (workstream 5) will be held in a community venue, accessible to participants. While we cannot specify the setting for the feasibility study to test the newly refined intervention (workstream 6) until it is developed, we expect it to be delivered in a suitable community venue. In all cases, participants will be given the option to engage with research activities over the telephone or a video platform if they have concerns about meeting a researcher or group face-to-face, or if they are unable to travel to a central venue.

### Eligibility (older people)

Surveys (workstreams 1 and 2) will be sent to patients at participating GP practices who are aged 65+, excluding those who have opted out of data sharing for research purposes, or who are on end-of-life care pathways. Participants approached to complete the surveys via community groups and through researcher face-to-face contact will be eligible if they are aged 65+ and are willing and able to take part.

Survey respondents who indicate their willingness to be contacted about further research activities on returning their surveys will be eligible to take part in one of: interviews (workstream 4); co-production workshops (workstream 5); or the feasibility study (workstream 6). However, we will exclude from these workstreams those who:

lack capacity to take part even with the help of a supporter, orhave no consultee available or willing to support involvement where they lack capacity to consent.

Language is not an exclusion criterion: where participants do not speak English, we will endeavour to provide translator support for interviews and workshops; alternatively, the support of a relative or friend who can help with translation will be sought.

### Eligibility (service providers)

Those providing digital training or support to older adults and who are independent of the research team will be invited to take part in our service scoping work (workstream 3) and the co-production workshops (workstream 5).

### Identification of digitally excluded older people

#### Workstream 1: survey

##### Design

A bespoke survey will incorporate elements necessary for modelling purposes. It will include relevant and appropriate internet usage questions from the Office for National Statistics annual survey (last use of the internet, frequency of use, use of internet for specific tasks),^25^ and known and potential predictors of digital exclusion (age, gender, partial postcode, living status (alone/with others), ethnicity).^36^,^9 26 27^ Layout and presentation of the survey will be informed by best practice (colour of paper, font size, etc) and we will be mindful of literacy levels and incorporate pictorial elements to maximise engagement. Patient and public involvement and engagement (PPIE) will support survey design, content and approach.

##### Outreach work

Prior to sending the surveys, we will identify older people’s community groups that fall within the catchment areas of participating GP practices, visiting them to explain the research and provide flyers for group attendees. Groups might include those organised by charities such as Age UK, informal community groups (eg, a lunch club, U3A), religious communities such as those attending a mosque or those at day centres or sheltered housing. This outreach work is intended to facilitate attendees’ engagement with surveys received later via their GP, as well as foster relationships for future in-person recruitment approaches.

##### Recruitment

A member of the clinical team at participating GP practices will identify eligible patients in their registers by running a prespecified search provided by the research team. Also included in the output of eligible patients will be a unique study ID, contact details, electronic Frailty Index (eFI) score (the eFI uses existing information held in electronic health records to measure frailty based on the accumulation of a range of deficits)^28^ and data items such as age, gender and postcode. These data will enable targeted telephone follow-up of non-responders to increase the representativeness of our sample.

GP practices will send via post to each eligible patient an introductory letter explaining what the study is about, followed 1 week later by: an invitation to participate, a participant information sheet (PIS), a survey and a ‘keeping in touch’ form on which participants can, optionally, provide their contact details if they wish to take part in later workstreams. They will also be sent a prepaid envelope for survey return directly to the research team. DocMail, a recognised secure method for contacting large numbers of patients for clinical purposes, will be used to minimise workload for GP practices, while retaining patient confidentiality. Those who do not wish to take part in the study will have a 2-week window following survey receipt to opt out from survey completion and any further study contact by returning the blank survey or telephoning the research team. Thereafter, we will augment our recruitment approach by a researcher based at each GP practice telephoning non-responders (an approach made clear in the PIS) to ask if they would be willing to complete the survey over the telephone. It will not be possible to follow-up all non-responders due to the volume of surveys sent, so the follow-up of participants will be prioritised using factors known to predict digital exclusion (eg, older age, female gender, socioeconomic deprivation derived from postcode, frailty).

Surveys will also be distributed by researchers directly to older people at community groups, clinics, day centres and sheltered housing—those engaged during the earlier outreach work—as well as via other community contacts across our recruitment catchment area including areas with varying levels of deprivation. Researchers will offer to administer surveys directly with community group members who are in attendance when they visit, offering support with survey completion (eg, providing language support, or reading questions for those with visual impairment). Researchers might also visit participating GP practices and geriatric medicine outpatient clinics to invite attending patients to complete the survey.

##### Data management and statistical analysis

GP practices will provide a list of study IDs with associated eFI scores to incorporate into the modelling work—an agreed approach enabling the research team to identify frailty status for survey respondents without obtaining any identifiable patient data. Index of Multiple Deprivation (IMD) will be derived from partial postcode (eg, AB99 1) entered by participants in the survey. We will compare demographic information of responders (eg, age, sex, eFI score) to that of the whole population of patients to whom surveys were sent. This whole population data will be obtained in summary form from the list of eligible participants generated at the practices.

A ‘hard’ definition of digital exclusion (ie,total non-use) will be used in the survey data analysis. Thus, participants will be defined as digitally included if they have independently (without help) performed one or more of the 22 online tasks specified in our survey, and digitally excluded if they have not performed any of these tasks. The tasks fall into four broad categories of online use: entertainment, healthcare, communication and buying things/managing money. However, we also wish to consider those who are narrow users and, as such, disadvantaged by not being able to fully engage with online activities.^10 18 26^ We will therefore also define participants as wide or narrow users, where wide users are those who perform one or more tasks in each of the four categories, and narrow users are those who do not perform at least one task in each category of use.

Summary statistics will be produced to describe prevalence of digital exclusion and narrow use. Logistic regression will be performed with digital exclusion as the binary outcome, with candidate predictors of digital exclusion being age, gender, IMD, ethnicity, frailty category and lone living status. Using a ‘multilevel analysis of individual heterogeneity and discriminatory accuracy’ (MAIHDA) approach,^29^ participants will be assigned to strata based on categories of the above predictors. For example, a strata might be white women aged 65–75 with mild frailty, living alone in an area with high levels of socioeconomic deprivation. The variance will be compared between the model with and without the strata random effect, which indicates whether there are interaction effects (known as intersectionality) between the variables. Using the MAIHDA, precision weighted estimates of digital exclusion can be produced for each strata, with the raw predictions being further weighted towards the fixed effect estimates as the strata size gets smaller. Should there be no evidence of interactions, we will revert to a fixed effects logistic regression model which would enable us to include different functional forms of the included predictors (eg, age as a continuous rather than categorical predictor), and to consider including other predictors (such as memory and sight problems). As a sensitivity analysis, we will also refit the model with narrow/wide use as the binary outcome. If sensitivity analysis shows similar characteristics of those who are non-users and narrow users, both would be included in our definition of digitally excluded used in later workstreams.

Data will be coded and analysed using statistical software Stata. The model will be sense-checked with participants during the interviews and workshops in workstreams 4 and 5, respectively.

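### IMD for the model comes from a survey partial postcode although the practice list holds each patient's postcode; this costs discrimination, precision and correct stratum assignment

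*Protocol article*

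**What the plan says.** The section on data management and statistical analysis for workstream 1 fixes the source of the deprivation variable: "Index of Multiple Deprivation (IMD) will be derived from partial postcode (eg, AB99 1) entered by participants in the survey". The same section lists IMD among the model inputs, with "candidate predictors of digital exclusion being age, gender, IMD, ethnicity, frailty category and lone living status", and says that MAIHDA strata are formed from categories of these predictors.

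Two other statements bear on this choice.

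- Under Recruitment, the practice search output for eligible patients includes study ID, contact details, the eFI score "and data items such as age, gender and postcode". Telephone follow-up of non-responders is then prioritised on factors that include "socioeconomic deprivation derived from postcode".
- In the data management section, a study-ID route from practice to research team exists for frailty: "GP practices will provide a list of study IDs with associated eFI scores to incorporate into the modelling work". Its stated purpose is to "identify frailty status for survey respondents without obtaining any identifiable patient data".

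The abstract and objective A say that the model is to work from primary care data and be usable in primary care systems. Workstream 2 reuses the workstream 1 survey methods for external validation.

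**The concern.** A truncated postcode of the kind given as the example covers many full postcodes, so it supports only one IMD value for a wider area. Small areas within it that differ in deprivation all receive the same value. The better measure can be derived from a postcode that the practice already holds, and a route for returning a practice-derived variable without identifiers is already agreed for eFI. The plan uses that route for frailty but not for deprivation.

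Three things are at stake.

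- **Discrimination and precision.** IMD is one of six candidate predictors. Averaging reduces its spread and hence the information that it carries.
- **Strata.** MAIHDA needs IMD in categories. Averaging pulls people towards the middle, so some residents of the most and least deprived small areas are placed in the wrong stratum.
- **Validation.** Because workstream 2 repeats the survey methods, it would repeat the same measurement and so would not show what was lost.

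**Working it through.** **The plan's own figure.** 6000 × 0.15 = 900 responses, as stated under Sample size. At 31% exclusion this is 900 × 0.31 = 279 events. The point disputes neither number, and the fix changes neither.

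**What has to be assumed.** The document does not say what share *w* of small-area IMD variance survives when the wider-area mean replaces the small-area value. I take *w* = 0.4, 0.5 and 0.7. I treat small-area deprivation as standard normal, written as area mean (variance *w*) plus an independent deviation (variance 1 − *w*). The correlation between the two measures is then √*w*.

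**Formulas**

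- Standard error of the IMD slope relative to small-area IMD: 1/√*w*, because the predictor's variance falls to *w*.
- Agreement on a median split: 0.5 + arcsin(√*w*)/π.
- Agreement on fifths: the probability that both values fall between the same two cut-points, with cut-points fixed on the small-area scale, summed over the five fifths by numerical integration.

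| *w* | SE inflation | Agreement, median split | Agreement, fifths | Most deprived fifth still classed there |
|---|---|---|---|---|
| 0.4 | 1.58 | 72% | 34% | 29% |
| 0.5 | 1.41 | 75% | 39% | 39% |
| 0.7 | 1.20 | 82% | 49% | 58% |

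**Which categorisation applies.** The plan fixes none: under Sample size, numbers per category and stratum are to drive it, with an aim of at least 10 people in every stratum. With 900 responses that allows at most 900/10 = 90 strata. Five IMD levels would leave 90/5 = 18 combinations for the other five predictors, yet two levels of each already make 2⁵ = 32. Two IMD levels give 2 × 32 = 64, which is within 90. A coarse split is therefore more likely than fifths, and the median-split column is the more relevant one.

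**Bias or lost information?** A simulation with an assumed log-odds of 0.5 per standard deviation of small-area deprivation, and 20% to 65% of variance lying within the wider areas (*w* = 0.80 to 0.35), gave:

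- continuous IMD: slope 0.49–0.50 with the area mean, against 0.50–0.51 with the small-area value, so almost unchanged;
- AUC from deprivation alone: from 0.636 to 0.622 at the mild end, and from 0.637 to 0.582 at the severe end;
- log-odds for the most deprived fifth against the rest: from 0.83 to 0.75, and from 0.86 to 0.55.

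Replacing a value by its area mean is Berkson-type error. It leaves a continuous slope nearly unbiased and costs discrimination and precision. Attenuation appears when IMD is categorised.

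**The case against.** **Deployment.** A reader might infer that the coefficient is fitted to one variable and will be applied to another. The document does not support that as a finding. It never says how IMD would be obtained when the model is used, and a postcode on record can be truncated to reproduce the fitted variable exactly. The mismatch is possible, not stated.

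**Contradiction.** A reader might also see two conflicting definitions of deprivation. They serve different purposes: one tells a practice-based researcher whom to telephone, the other belongs to a research dataset meant to hold no identifiable patient data. The choice can be improved, but the text does not contradict itself.

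**Size.** Every magnitude above depends on an assumed variance share, and the figures for fifths also depend on a categorisation that the plan does not specify. The AUC loss is for deprivation alone; the loss in a model with six predictors is not quantified. All of this stands.

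**Privacy.** Avoiding identifiable data is a good reason not to export full postcodes. It is no reason against exporting an IMD category by study ID, which is no more identifying than the eFI score already sent. This objection fails.

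**Community recruits.** People surveyed at groups, clinics, day centres or sheltered housing may not be linkable to a practice list, and the survey partial postcode is the one source that covers everybody. Using it only for them would mix two measures, split by recruitment route, which may itself relate to digital exclusion. The force of this is limited, because the same people also lack the eFI link. Still, it means that the fallback needs a source flag and a sensitivity analysis.

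**Conclusion.** The point holds as a design weakness with an inexpensive remedy. The model uses the coarser of two available deprivation measures, although the practice holds the finer one's source and a non-identifying route exists to pass it on. The consequence is lost discrimination and precision for IMD, and misclassification when IMD is categorised for the strata. It is not a materially biased continuous slope.

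The document does not allow the size to be computed. With 40–70% of small-area variance retained, the standard error of the IMD effect rises about 1.2–1.6 times. Agreement with the small-area category is about 72–82% on a median split and 34–49% on fifths. The fifths figures should not be read as a statement that most people will be misclassified in this study, since the planned sample probably cannot carry five IMD levels in the strata.

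**What to change.** - Have each practice derive an IMD category from the full postcode on its own system and return it with the study-ID and eFI list. No postcode leaves the practice.
- Use that category as the IMD predictor in the model in both workstream 1 and workstream 2.
- Keep partial-postcode IMD only for respondents who cannot be linked, and record the source of IMD for every respondent.
- Add a sensitivity analysis: either restrict to linked respondents, or use partial-postcode IMD for everyone.

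**Cost.** One extra non-identifying data item, a postcode look-up at the practice, the practices' agreement to the added item, and a protocol modification through the approval route described under Ethics. Participants do nothing more, and no sample-size figure changes.

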#### Data management and analysis

We will apply the model developed in workstream 1 to predict which older people are digitally excluded. Using the survey responses, we will compare these predictions to the reported digital exclusion status of participants. Predictive performance statistics will be used to produce optimism-adjusted estimates for calibration (eg, calibration-in-the-large, observed/expected), discrimination (eg, area under the curve) and overall (eg, Nagelkerke R^2^) performance of predicted risks.

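### The narrow-user class, as defined, takes in the non-users, which biases the check on whether narrow users resemble non-users towards merging the two groups

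*Protocol article*

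**What the plan says.** All of this is in the protocol article, mainly under Workstream 1, Data management and statistical analysis.

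- **Main outcome.** Anyone who has done even one of the 22 listed tasks unaided counts as included. Everyone else falls on the other side of the line: a respondent is "digitally excluded if they have not performed any of these tasks".
- **Second classification.** "We will therefore also define participants as wide or narrow users": the split covers participants, not only those who go online. "wide users are those who perform one or more tasks in each of the four categories", whereas "narrow users are those who do not perform at least one task in each category of use". The requirement that tasks be done without help is not repeated here.
- **Refit and decision rule.** As a sensitivity analysis the model is refitted with narrow/wide use as the binary outcome. No step removes non-users first. Then: "If sensitivity analysis shows similar characteristics of those who are non-users and narrow users, both would be included in our definition of digitally excluded", for use in the later workstreams.
- **Downstream use.** Workstream 6, Sampling, selects digitally excluded people under a definition to be informed by the workstream 1 analysis. Workstream 2, Data management and analysis, states: "We will apply the model developed in workstream 1 to predict which older people are digitally excluded".

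**The concern.** The definition and the decision rule do not fit together. The rule treats non-users and narrow users as two groups that might or might not be pooled. The definition makes narrow the complement of wide, so one group lies almost wholly inside the other. A model of narrow versus wide then has the non-users among its events, and comparing it with the non-use model is partly a comparison of the non-users with themselves.

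The question the rule needs answered is whether people who do some things online, but not in all four categories, share the profile of people who do nothing. The refit as described does not isolate that group. What is at stake is the definition of digital exclusion carried forward, expressly for eligibility in the feasibility study. If narrow users have a different profile, the planned check may not show it.

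**Working it through.** **1. Who is narrow under the stated rule**

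| Respondent | Main outcome | Wide/narrow |
|---|---|---|
| No task at all | Excluded | Narrow |
| Some tasks alone, not in all four categories | Included | Narrow |
| At least one task alone in each category | Included | Wide |
| Tasks only with help, not in all four categories | Excluded | Narrow |
| Tasks only with help, in all four categories | Excluded | Wide if helped tasks count, otherwise narrow |

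Apart from the last row, everyone excluded is also narrow.

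**2. Inputs**

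- From Workstream 1, Sample size: 15% of 6000 = 0.15 × 6000 = 900 responses, which reproduces the article's figure. With 31% digitally excluded, 0.31 × 900 = 279 non-users and 621 users.
- Assumed, because the article gives no figure: the share q of users who are narrow, taken as 20%, 40% and 60%.
- Assumed for illustration: among users, narrow use is unrelated to the predictor, so the users-only odds ratio is 1.0.
- The exception in the last row of the table is ignored.

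**3. Make-up of the narrow class**

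Narrow proportion = 0.31 + 0.69q. Share of it who are non-users = 0.31 / (0.31 + 0.69q).

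- q = 20%: 0.31 / 0.448 = 69%
- q = 40%: 0.31 / 0.586 = 53%
- q = 60%: 0.31 / 0.724 = 43%

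**4. Effect on the odds ratio**

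Take a standard-normal predictor x. The chance of non-use is p(x), logistic in x, with the intercept set so that prevalence is 31%. The chance of being narrow under the stated rule is p(x) + (1 − p(x))q. A logistic model fitted to that outcome gives:

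| Odds ratio for non-use | q = 20% | q = 40% | q = 60% | Users only |
|---|---|---|---|---|
| 1.5 | 1.32 | 1.23 | 1.18 | 1.0 |
| 2.0 | 1.58 | 1.41 | about 1.3 | 1.0 |
| 2.5 | 1.80 | 1.55 | 1.41 | 1.0 |

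Every entry under the stated rule exceeds 1.0 although narrow use has no association with the predictor among users.

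**5. At the planned sample size**

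A second simulation used 900 respondents and three predictors with odds ratios of about 1.64, 1.50 and 1.42 for non-use, with partial users again unrelated to all three. Here the narrow-but-using group is given as a share of all respondents.

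| Narrow-but-using | Odds ratios, stated rule | All three same direction as non-use | All three also significant |
|---|---|---|---|
| 10% | 1.43, 1.34, 1.31 | 100% of runs | 95% |
| 20% | 1.32, 1.27, 1.22 | 100% | 72% |
| 30% | 1.26, 1.21, 1.18 | over 99% | 48% |
| 40% | 1.22, 1.17, 1.14 | 98% | 20% |

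Among users only, all three were significant in the same direction in none of the runs. Significance of all three is only one possible reading of similarity; it is not the article's criterion.

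The pull can also hide an opposite profile. With true users-only odds ratios of 0.85, 0.88 and 0.90 and narrow-but-using respondents at 20%, the stated rule still gave 1.21, 1.18 and 1.15.

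**The case against.** The best defence is that separate groups are plainly intended. The decision rule names non-users and narrow users side by side, the prevalences of exclusion and narrow use are to be described as two things, and Workstream 4, Sampling, lists regular, limited and non-users. On that view a qualifier such as 'among users' was lost in a condensed article. This is a fair reading of intent and it bears on severity. It does not remove the point, because the article does state a rule, the rule covers participants, and followed as written it gives the nested comparison.

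Second, the overlap does not settle the result. An odds ratio of 2.0 falls to between about 1.3 and 1.6, which an analyst might well call dissimilar, and the article gives no criterion for similarity. That stands: the supportable statement is a bias towards similarity, not a foregone merge. The illustration also rests on an assumed narrow-use share and on no association among users.

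Three stronger readings are tempting and are not supported.

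- A reader might infer that every non-user is narrow. The independence condition is missing from the wide/narrow rule, so someone helped in all four categories could be both excluded and wide.
- A reader might infer that, after a merge, workstream 2 would test a non-use model against a wider outcome and so appear miscalibrated. Under the literal definition the narrow/wide refit is already a workstream 1 model of essentially the merged outcome, and nothing says that the non-use model would be validated against the wider one.
- A reader might infer that calling the outcome total non-use makes its coding uncertain, since people who go online only with help count as excluded. The operational rule that follows is explicit, so only the label is loose.

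**Conclusion.** The point holds as a should-fix. The stated narrow class contains the non-users, with the one possible exception above, and the comparison that decides the merge is therefore biased towards finding the groups alike. For a predictor with odds ratio 2.0 for non-use, the spurious association in the refit is about 1.6, 1.4 or 1.3 when 20%, 40% or 60% of users are narrow, against 1.0 among users. These sizes depend on the 31% prevalence, which is the article's, and on the narrow-use share and the lack of association among users, which are assumptions. The direction of the pull follows from the nesting itself.

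The main outcome, its prevalence estimate and the main model are unaffected. The consequence is confined to the definition carried into later workstreams, expressly eligibility for workstream 6.

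**What to change.** 1. Define three mutually exclusive classes with the same independence condition throughout: no independent use; narrow, meaning at least one task done independently but not in all four categories; wide, meaning at least one task done independently in each category.
2. Base the merge decision on narrow versus wide fitted among users only, or on one multinomial model with wide use as reference that compares the narrow and non-use coefficients.
3. State that, if the definition is widened, the workstream 1 model carried into workstream 2 is the one fitted to the widened outcome.

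The cost is a change of wording and one model on data already collected. The users-only contrast has 0.69 × 900 = 621 respondents, so its intervals are wider. As a rough guide, taking information as n × p × (1 − p):

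- 20% of users narrow: 900 × 0.448 × 0.552 = 223 against 621 × 0.2 × 0.8 = 99, a standard error about 1.5 times as large.
- 40% narrow: 218 against 149, about 1.2 times.
- 60% narrow: 180 against 149, about 1.1 times.
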